**Methods:** This 6-month study will adopt a one-arm mixed method type 3 implementation-effectiveness hybrid design and be conducted in a single clinical site, the Chronic Viral Illness Service of the McGill University Health Centre. It will be guided by tools of implementation science (e.g., frameworks, outcomes). Five HIV physicians and 30 of their HIV patients will participate. The intervention will involve having patients complete the I-Score with an adapted version of the Opal smartphone app, prior to meeting with their physician. Both the patient and the physician will have access to the I-Score results, for consideration during the clinic visits at Time 1 (T1), T2 (3 months), T3 (6 months). The implementation strategy will focus on patient and provider involvement, education, and training, as well as on promoting the intervention's adaptability. The strategy's cornerstone will be the hiring of an Application Manager to facilitate implementation. Implementation, patient, and service outcomes will be collected (T1, T2, T3). The primary outcome of this pilot study is the intervention's acceptability (target: mean scale score of 4 on 5). Qualitative data obtained through provider focus groups (T2, T3), patient interviews (T2, T3) and the Application Manager's field notes (T1-3) will serve especially to evaluate the implementation strategy and inform any methodological adaptations.

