### *The I-Score intervention*

During the study, participating patients will visit with their HIV physician three times, at Time 1 (T1), month 3 (T2), and month 6 (T3), prior to which they will complete the I-Score, as instructed. This visit schedule was selected as it fits within guidelines for the clinical follow-up of HIV in Quebec (Ministère de la santé et des services sociaux, 2019), while maximizing the collection of repeated study measurements. Given COVID-19, one visit (T2) will be done remotely (by phone or teleconferencing), while the other visits will be held at the CVIS. The I-Score PROM contains 20 items, covering 6 domains of barriers to ART adherence. Respondents indicate how often each barrier made adherence difficult in the past 4 weeks, with a continuous scale, from never to always. [Additional details on measure scoring and interpretation will be provided to the REB as they become available]. For details on the measure's development see Engler et al., 2018, Engler et al., 2019, Lessard et al., 2019, Toupin et al., 2018.

The core intervention of this pilot consists of having individuals with HIV on ART register on the Opal app and complete the I-Score PROM prior to each of three consecutive visits with their HIV physician. The patients will receive a reminder to complete the I-Score one week before their visit and they will have immediate access to their results. The HIV physician will acquire the I-Score results before each visit via the ORMS dashboard, an appointment and questionnaire management tool integrated with Opal and designed specifically for healthcare providers. The option of graphically presenting scores over time will also be available, allowing physicians and patients to compare past and present scores. It is expected that patients and physicians will review the I-Score results so they can be considered during the clinic visit (see Figure 1).

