### *Feasibility*

Feasibility relates to the extent to which our I-Score intervention is successfully used or carried out within the study site (Proctor et al., 2011). To determine feasibility, data will be collected on the Consent rate, defined as the proportion of approached eligible patients and physicians who consent to participate. Individuals who choose not to participate will be asked to provide select sociodemographic information (sex, year of birth, preferred language) and their reason(s) with a checklist on a refusal form (see the Appendix). If 70% or more agree to participate, the study will be judged feasible on this aspect. We will also examine the Retention rate, indicated by the proportion of patients and physicians who complete the study. Eighty percent will be considered the benchmark for success. Missing I-Score data rates due to network failure as well as patient and provider non-completion of self-reported questionnaire data will be calculated as well. The criterion for success on this metric is at least 90%. Furthermore, participants will complete the Feasibility of Intervention Measure (Weiner et al.,

2017), at T1, T2 and T3, a four-item self-report measure that is appropriate for different stakeholder groups (e.g., patients, providers). Example items include “This [evidence-based practice] seems possible” and “This [evidence-based practice] seems doable.” Average scores of at least 4, indicative of agreement on the 5-point response scale, will signify the I-Score intervention’s feasibility.

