## **Data analysis**

### **Quantitative analysis**

Time 1 questionnaires for people living with HIV and for HIV physicians will be summarized with descriptive statistics. For continuous variables, the minimum, the maximum, the mean, and the standard deviation will be reported. For ordinal and nominal qualitative variables, we will report absolute and relative frequencies (proportions).

As, specified, for most quantitative metrics relating to Objectives 1 and 2, as recommended for pilot studies, score targets were set to evaluate the ability to proceed to a definitive trial (Thabane et al., 2010). For people living with HIV and HIV physicians, continuous outcomes expressed on a Likert scale will be summarized with the minimum, the maximum, the mean, and the standard deviation at T1, T2 and T3. Binary outcomes (yes or no) will be reported with absolute and relative frequencies (proportions) at T1, T2 and T3. The means and proportions of T1, T2 and T3 will be confronted with their corresponding thresholds for success, presented in Table 2. To study the tendency of means and proportions for people living with HIV over time, a Linear Mixed Model (LMM) or a

Generalized Linear Mixed Model (GLMM) will be used, for continuous and binary outcomes, respectively. The response variable of each model will be the corresponding outcome and the independent variable will be the time (T1, T2 and T3). The null hypothesis of no time effect on the corresponding outcome will be tested with a Student's t-test on the regression coefficient. If the null hypothesis is rejected, we will perform post-hoc Student's paired t-tests between all combinations of time points to show between which time points means and proportions differed significantly. Additionally, to verify if each threshold for success is met at the end of the study, we will test the null hypothesis that each mean or proportion at T3 is inferior to its corresponding threshold with a Student's t-test. For all analyses, a significance level of 5% will be adopted. Finally, where appropriate, Cronbach's alpha will be calculated to evaluate the internal consistency of subscales.

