Regarding the patient outcomes of Objective 3, barriers to adherence and adherence will be summarized with the minimum, the maximum, the mean, and the standard deviation. Viral load will be reported by absolute and relative frequencies, as it is considered a dichotomous variable. For the service outcome obtained from the physician checklist, we will report the proportion of clinic visits when physicians took action based on the I-Score results, among the visits where an adherence barrier of concern was identified by physicians. Proportions will be reported for T1, T2 and T3 and globally, across time periods. To evaluate evidence of a statistically significant difference in our chosen effectiveness outcomes, we will run a Student's paired t-test for barriers to adherence and adherence and a McNemar test for viral load, between T1 and T3. To complete the analysis of the service outcome, we will use a logistic regression model, considering only the visits where an adherence barrier of concern was identified by physicians. The dependent variable is the binary variable of whether or not an action was taken by physicians and the independent variable is the time, considered as a factor with three independent levels (T1, T2 and T3). We will test the null hypothesis that time has no effect on the probability of taking action, with a t-test on the regression coefficient. We will conclude the analysis by testing the null hypothesis of equality of proportions between all pairwise combinations of time points, with a Student's t-test between two proportions, performing a Bonferroni correction for multiple tests. For all analyses, a significance level of 5% will be adopted.

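### The test of change over time for patient outcomes uses one coefficient for a three-visit hypothesis, so under numeric coding of time a shift confined to T2 is missed and the pairwise comparisons usually stay closed

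*Protocol*

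**What the plan says.** Protocol, Quantitative analysis, first part (Objectives 1 and 2). Outcomes of people living with HIV are modelled with a linear mixed model if continuous and a generalized linear mixed model if binary. In each model "the independent variable will be the time (T1, T2 and T3"). The text does not say whether time is a number or a factor. The null of no time effect "will be tested with a Student's t-test on the regression coefficient", with coefficient in the singular. The next step is conditional: "If the null hypothesis is rejected, we will perform post-hoc Student's paired t-tests between all combinations of time points".

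Protocol, Quantitative analysis, second part (Objective 3). For the service outcome (whether the physician took action), time is "considered as a factor with three independent levels (T1, T2 and T3"). The null is nevertheless again tested with a t-test on one coefficient. The pairwise comparisons there carry a Bonferroni correction and no stated gate.

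Protocol, The I-Score intervention. Of the three visits, "one visit (T2) will be done remotely (by phone or teleconferencing"); T1 and T3 take place at the clinic.

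**The concern.** The stated null is that the outcome does not change over three visits: mean(T1) = mean(T2) = mean(T3). That is two independent equalities, so a test of it needs two degrees of freedom. The protocol names a test with one.

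The comparisons meant to show which visits differ, including T1 with T2 and T2 with T3, open only when that single test rejects. If the test cannot see T2, the gate can stay shut when T2 is the visit that differs.

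A pattern specific to T2 is plausible in this design. T2 is the only remote visit, and stakeholder feedback collected from T2 feeds cyclical changes to the implementation before T3. A problem present at T2 and corrected by T3 is one such pattern.

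At stake is the formal inference on change over time, and whether the pairwise tests are run, for patient outcomes collected at all three visits. The consent rate is collected only at T1 (Table 3), so it has no time trend and is outside this point.

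**Working it through.** The protocol gives no SD, effect size or power for the time test, so there is no planned figure to reproduce.

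**Inputs from the protocol.** Three visits, at baseline, month 3 and month 6 (equally spaced). Sample size: "Five HIV physicians and 30 of their HIV patients will participate" (Summary), so n = 30 patients. For retention, "Eighty percent will be considered the benchmark for success" (Feasibility), so n = 0.80 × 30 = 24 if that benchmark is just met. Significance level 5%.

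**Assumptions, not in the protocol.** Two-sided test, complete data, equal variances, within-patient correlation ρ of 0.3, 0.5 or 0.7, and shifts of 0.5 or 0.8 SD. If the Acceptability E-scale had an SD of 4, 0.5 SD would be 2 points.

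**Step 1: what a single slope sees.** Code the visits −1, 0, 1. With complete data the slope estimate is Σx·ȳ / Σx² = (ȳ3 − ȳ1)/2. The T2 mean has weight zero.

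**Step 2: a 0.5 SD shift at T2 only, T3 back at the T1 level, n = 30, ρ = 0.5.**
- Squared deviations of the visit means from their average: Σ(μj − μ̄)² = 0.5² × 2/3 = 0.1667.
- Joint test: noncentrality n·Σ(μj − μ̄)²/(1 − ρ) = 30 × 0.1667/0.5 = 10. An F test on 2 and 58 degrees of freedom then has power of about 79% to 80%.
- Slope test: noncentrality 0. The unmodelled shift goes into the residual, whose expected mean square rises by (59 + 10)/59 = 1.17. Rejection therefore falls below 5%, to 3.4% by simulation.
- In the same setting the T1–T2 paired t-test would be significant in about 75% of runs. In about 73% of runs it would be significant but blocked by the gate.

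**Step 3: other n and ρ, full recovery by T3 (simulated, 40,000 runs per cell).** Entries run across ρ = 0.3 / 0.5 / 0.7.

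| n | Shift | Slope test | Joint test |
|---|---|---|---|
| 30 | 0.5 SD | 3.8% / 3.4% / 2.6% | 64% / 80% / 95% |
| 30 | 0.8 SD | 2.6% / 2.0% / 1.1% | 97% to 100% |
| 24 | 0.5 SD | 3.9% / 3.4% / 2.6% | 53% / 69% / 89% |
| 24 | 0.8 SD | 2.5% / 2.1% / 1.1% | 92% to 100% |

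**Step 4: other patterns, n = 30, ρ = 0.5, 0.5 SD.** The slope's own noncentrality is n(μ3 − μ1)²/[2(1 − ρ)].

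| Pattern (T1, T2, T3) | Slope noncentrality | Slope test | Joint test |
|---|---|---|---|
| Half recovery (0, −0.5, −0.25) | 30 × 0.0625/1 = 1.875 | 24% | 66% |
| Persistent (0, −0.5, −0.5) | 30 × 0.25/1 = 7.5 | 76% | 79% |
| Exactly linear (0, −0.25, −0.5) | 30 × 0.25/1 = 7.5 | 77% | 66% |

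**Step 5: time as a factor.** There are now two coefficients, for example T2 against T1 and T3 against T1. For the T2-only 0.5 SD shift (n = 30, ρ = 0.5), a t-test on the T2 coefficient rejects 77% of the time and one on the T3 coefficient 5%. The protocol does not say which is meant.

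**Step 6: binary outcome, rough check.** With assumed proportions of 85%, 60% and 85% and n = 30, the slope test rejects about 7% and the joint test about 76%. This used about 600 runs and a marginal logistic model in place of the mixed model, so it shows direction only.

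**The case against.** **A dip at T2 would not go unseen.** A reader might infer that it would simply be reported as no time effect. The protocol does not support that. It also requires summaries at T1, T2 and T3 and compares each visit's value with its success threshold. With assumed acceptability means of 25, 23 and 25 against the threshold of 24, the planned table would show T2 below target whatever the time test says. The T2 interviews and focus groups and the Application Manager's notes look for problems there too. This stands.

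**The primary target and the decision to proceed are not affected.** A reader might infer that they are, because acceptability is one of the outcomes modelled. The thresholds are tested at T3 separately from the time model. This stands.

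**Numeric coding is an inference.** It rests on the singular coefficient, and listing the three visits also fits a factor. This stands, but factor coding does not rescue the text: there are then two coefficients and no statement of which one is tested.

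**The lowest detection rates belong to one pattern.** They require full recovery by T3. It would be wrong to conclude that T2 departures in general go undetected or that the pairwise tests never open: the gate opens occasionally even with full recovery, and often when T3 also differs from T1. This stands.

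**A slope is a legitimate test of trend.** The protocol speaks of studying tendency, and if change is assumed linear a zero slope does mean no time effect. That assumption is not stated, however, and the follow-up compares every pair of visits, which goes beyond a trend question.

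**A T2 shift may be less likely than it looks.** Patients complete the I-Score in the same app before every visit, so the tool they rate does not change when the visit is remote. This lowers the likelihood but does not remove it.

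**Such detail belongs in a statistical analysis plan.** Much of it could. Here the protocol itself fixes the null, the test and the gate, so the point concerns what is stated.

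**Conclusion.** The point holds in a limited form. For patient outcomes measured at all three visits, the stated test does not in general test the stated null, and the pairwise comparisons depend on it.

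Under numeric coding, a T2-only shift that has fully recovered by T3 is detected about 1% to 4% of the time, against 53% to 100% for a joint test. With half recovery the contrast is about 24% against 66%, and with a persistent shift about 76% against 79%. Under factor coding the outcome turns on an unspecified choice of coefficient, which could be made after the data are seen. The Objective 3 service-outcome model shows this mismatch explicitly, with less consequence because its pairwise tests are not gated.

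These figures rest on the assumptions listed with the working, none of which the protocol supplies. The damage is confined to the formal inference on change over time and the opening of the pairwise tests. The text should be corrected, but the pilot's main conclusions do not depend on it.

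**What to change.** In the Objective 1 and 2 text of Quantitative analysis, state that time enters as a three-level factor. Test the null with a joint two-degree-of-freedom F, Wald or likelihood-ratio test, and make that test the gate for the pairwise comparisons. In the Objective 3 text, keep the three-level factor and replace the t-test on one coefficient with the same kind of joint test.

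This is about one sentence in each place and needs no new data. The cost is some power when the true change is exactly linear: about 66% instead of 77% for a total change of 0.5 SD at n = 30 and correlation 0.5.

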### Setting and participants

The study setting is a large hospital-based clinic in Montreal, Quebec, Canada. This clinic, the Chronic Viral Illness Service (CVIS) of the MUHC, offers multidisciplinary care to approximately 2000 adults living with HIV. Five physicians treating individuals with HIV at the CVIS will be recruited to participate as well as 30 of their adult patients. This sample size amply meets rule of thumb recommendations for one-arm pilot studies (Sim & Lewis, 2011). Patients must be confirmed HIV-positive, have a history of known or suspected adherence problems in the past year, be aged at least 18 years old, be on or beginning combination ART, be literate in English or French, and own a smartphone. Full details on eligibility are presented in the next section. Ten female patients will be recruited, to ensure sufficient representation of women living with HIV (Public Health Agency of Canada, 2018).

[figure not shown]

Figure 3. Pilot study design.

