## Objective 1 -Evaluate perceptions of the I-Score intervention

### *Acceptability*

The primary outcome of this pilot study will be acceptability, as measured by the Acceptability E-scale (AES) for web-based PROMs (Tariman et al., 2011). *Acceptability* is related to how agreeable, palatable, or satisfactory an intervention is perceived to be by stakeholders (Proctor et al., 2011). It will be measured, at T1, T2, and T3, with an adapted version of the AES for administration to both patients and physicians in the study. The scale has 6 items rated on a 5-point Likert scale that varies depending on the item. Example items of the original measure include “How would you rate your overall satisfaction with this computer program?”, and “How easy was this computer program [...] for you to use?” A summary score is obtained by adding the item scores (range: 6-30). A score of at least 24 (80% of maximum) indicates high acceptability and usability, as suggested by the scale developers.

Acceptability will also be measured at T1, T2 and T3 with a variant of the Net Promoters Score (NPS) used by England’s National Health Service (NHS) and labelled the Friends and Family Test (NHS, 2014). The NPS is considered a measure of user satisfaction (Hamilton et al., 2014). A single question will be asked (“How likely are you to recommend the I-Score?”) and rated on a 5-point Likert scale (1 = Extremely unlikely, 2 = Unlikely; 3 = Neither likely nor unlikely; 4 = Likely; 5 = Extremely likely). From this measure, the percentage recommending the I-Score will be calculated (score of 4 or 5), with a success threshold of 80% or more. An NPS-type score will also be calculated by creating three groups: promoters (score of 5), passives (score of 4), and detractors (score of 1-3). Subtracting the percentage of detractors from the promoters provides the NPS. NPS scores range from -100 to 100. A positive score (> 0) will be considered good (Stirling et al., 2019), and a score of  $\geq 50$ , excellent.

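### The T3 success test uses only patients observed at T3, although the mixed model planned beside it could bring in T1 and T2; score-related dropout can bias the primary result upward

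*Protocol*

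**What the plan says.** The Acceptability section names the primary outcome: "The primary outcome of this pilot study will be acceptability, as measured by the Acceptability E-scale (AES) for web-based PROMs". The scale is given to patients and physicians at T1, T2 and T3. The target is fixed there too: "A score of at least 24 (80% of maximum) indicates high acceptability and usability, as suggested by the scale developers". The Summary gives the same target as an item mean of 4 on 5.

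The Quantitative analysis section then does three things with the repeated metrics.

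- It sets the T1, T2 and T3 means and proportions descriptively against their thresholds.
- It fits a linear or generalised linear mixed model to the patients' data, with time as the only independent variable. The model's sole stated use is to test for a time effect. If that test rejects, it is followed by "post-hoc Student's paired t-tests between all combinations of time points".
- It runs the formal end-of-study check, a Student's t-test at the 5% level of the null hypothesis that "each mean or proportion at T3 is inferior to its corresponding threshold". The model is not linked to this test.

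On retention, the Feasibility section says: "Eighty percent will be considered the benchmark for success". Under Study metrics and instruments, a missed threshold means that modifications are needed before a definitive trial.

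**The concern.** The formal success test can use only patients who have a T3 value. A patient who scores the I-Score low at T1 or T2 and then leaves does not enter it, although those scores are in hand and the model in the same paragraph could use them.

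The primary outcome is satisfaction with the tool, so a link between low scores and leaving is plausible. If it exists, the T3 mean of those who remain is too high. A threshold that appears to be met removes the prompt to modify the intervention before the definitive trial, which is the decision the pilot is meant to inform.

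This is not a complaint about missing-data detail that may sit in an unseen statistical analysis plan. The protocol itself names the test for the success decision.

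**Working it through.** **Inputs from the protocol.** 30 patients and 5 physicians; scale range 6 to 30, six items; target mean 24; retention benchmark 80%; significance level 5%. The null hypothesis is directional, but sidedness is not stated. The sample size rests on a rule of thumb ("This sample size amply meets rule of thumb recommendations for one-arm pilot studies"), so the protocol gives no SD, correlation or dropout model. These are assumed below and varied.

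**Step 1. Reproduce the target.** 0.80 × 30 = 24, and 4 × 6 items = 24. The two statements agree.

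**Step 2. Loss tolerated.** 0.80 × 30 = 24 patients and 0.80 × 5 = 4 physicians. Six patients may be missing at T3 with retention still judged a success.

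**Step 3. Bias by arithmetic.** Bias of the observed mean = dropout share × (mean of those who stay − mean of those who leave). If those who stay average exactly 24:

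| Loss | Leavers lower by | Bias | All-patient mean |
|---|---|---|---|
| 10% | 2 | 0.2 | 23.8 |
| 10% | 8 | 0.8 | 23.2 |
| 20% | 2 | 0.4 | 23.6 |
| 20% | 4 | 0.8 | 23.2 |
| 20% | 6 | 1.2 | 22.8 |
| 20% | 8 | 1.6 | 22.4 |

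**Step 4. Error rate of the formal test.** Simulation of n = 30 with three normal scores, true mean 24 at each visit, SD 4 and correlation 0.6. Patients may leave after T1 or T2 with a probability that rises as the last observed score falls (1 to 2 logits per SD), and 82% are retained.

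- Observed T3 mean: about 24.4 to 24.6, so bias is about +0.4 to +0.6.
- One-sided 5% t-test: rejects in about 12 to 19% of trials.
- Likelihood estimate of the T3 mean using T1 and T2: 24.0.

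**Step 5. Other assumptions.** A second simulation has about 21% loss, with dropout depending on one score at 1.5 logits per SD. The true mean is 24, SD 4 and correlation 0.6.

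| Dropout depends on | Observed T3 mean | One-sided rejection | Likelihood T3 mean |
|---|---|---|---|
| nothing (random) | 24.02 | 5.4% | 24.02 |
| T2 score (seen) | 24.57 | 17.8% | 24.00 |
| T3 score (unseen) | 24.96 | 35% | 24.58 |

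With dropout on the T2 score, bias is +0.44, +0.57 and +0.72 for SD 3, 4 and 5. At SD 4, rejection is 11% for correlation 0.4 and 23% for correlation 0.8.

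**Step 6. When the true mean is below target.** The protocol has two comparisons, and they behave differently. With 24 patients and SD 4, the formal one-sided test needs an observed mean of about 24 + 1.714 × 4/√24 = 25.40, whereas the descriptive comparison needs only 24. Under the Step 4 mechanism with a true mean of 23.5:

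| Dropout | Observed mean ≥ 24 | Formal one-sided test passes |
|---|---|---|
| 1 logit per SD | 45% | 3.6% |
| 2 logits per SD | 56% | 6.6% |
| random | about 26% | 1.4% |

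The model-based mean reaches 24 in about 27% of trials, close to the rate under random dropout.

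**The case against.** **Nothing says the leavers will be the dissatisfied ones.** This is correct. The protocol makes no such prediction, and 80% is a minimum for success, not an expected loss. Patients must be willing to download the app and are paid for questionnaires at three times. Under random dropout the bias is nil. The point is therefore conditional.

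**T1 and T2 are not ignored.** The T1 and T2 means are also compared with the threshold, retention has its own criterion, and patient interviews begin at T2. Dropout would be visible beside the T3 result. This stands: reliance on T3 alone is true of the formal test, not of every comparison.

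**The effect on the formal test is modest below the target.** This also stands. A reader might infer that a pilot with a truly inadequate mean would be declared a success in more than half of trials. The 56% belongs to the descriptive comparison of means under a steep assumed dropout mechanism. In that setting the formal test passes in 6.6%.

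**The T1-to-T3 paired tests.** A reader might infer that these also inflate acceptability. They do not. The protocol specifies "a Student's paired t-test for barriers to adherence and adherence" and a McNemar test for viral load, all Objective 3 outcomes, and viral load is not collected at T2. For acceptability, the post-hoc paired tests cover every pair of visits, T2 included.

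**The remedy has limits.** The planned model covers patients only. It removes just part of the bias when dropout depends on the unseen T3 score. A generalised linear mixed model gives patient-specific probabilities, which must be averaged over patients before comparison with 80%, and it can be unstable with 30 patients. All of this is right, and it is why a sensitivity analysis is needed as well.

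**Conclusion.** The point holds in a limited form. The formal T3 test discards T1 and T2 information that a model planned in the same paragraph could use, while a loss of up to 20% counts as success. If dropout follows low observed scores, the primary mean is biased upward by about 0.4 to 0.6 points and the one-sided error rate at a true mean of 24 rises from 5% to about 12 to 19%. This assumes SD 4, correlation 0.6 and about 18% loss; none of these comes from the protocol. With no link between score and dropout, there is no bias.

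The documents do not support the claim that acceptability will be inflated, only that it can be. It is worth correcting because the correction is cheap and the outcome is the primary one.

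**What to change.** - **Continuous patient metrics** (Acceptability E-scale, appropriateness and feasibility measures): fit the planned linear mixed model with time as a three-level factor to all available visits. Compare its T3 mean and confidence interval with the threshold, and state whether the test is one-sided.
- **Percentage recommending**: use the planned generalised linear mixed model and report the marginalised T3 proportion.
- **Alongside**: show the result from patients observed at T3, and a sensitivity analysis with leavers scoring lower (for example by the 2 to 8 points in the working) or counted as not recommending.
- **Physicians**: keep the descriptive T3 result and state how many of the five contributed.
- **Separate and minor**: take the T3 minus T1 change in I-Score and self-rated adherence from the same kind of model, so that T2 and incomplete pairs contribute. This does not bear on acceptability.

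**Cost.** A change of analysis wording and some extra programming for the marginalised proportions; no new patients, visits or data. The model estimate assumes that dropout depends only on observed scores. That is weaker than what the observed-at-T3 test needs, but it is still an assumption.
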